#### Mediating variables

All students will complete a battery of self-report measures of psychological variables based on the trans-contextual model. These factors are expected to reflect the mechanisms by which the intervention affects change in the primary outcome consistent with the model.

##### Students’ perceived autonomy support by their PE teacher

Perceived autonomy support from PE teacher will be measured using items from the perceived autonomy support scale for exercise settings [44]. The scale consists of 18 items (e.g., “I feel that my PE teacher provides me with choices and options to …”) and responses are provided on 7-point scales (1 = *strongly disagree* and 7 = *strongly agree*). The scale has demonstrated adequate construct validity and reliability statistics in previous research [44, 45].

##### Autonomous motivation, controlled motivation and amotivation toward in school and out-of-school physical activity

Autonomous and controlled forms of motivation for in-school and out-of-school activities will be measured using a modified version of the perceived locus of causality questionnaire [46], and amotivation using modified version of amotivation subscale from the sport motivation scale [47]. The total scale consists of ten items with two items measuring each of the external regulation (e.g., “I do PE/ physical activity so that the teacher won’t yell at me”), introjected regulation (e.g., “I do PE/physical activity because I would feel bad if the teacher thought that I was not good at PE”), identified regulation (e.g., “I do PE/physical activity because it is important to me to do well in PE/physical activity”), intrinsic regulation (e.g., “I do PE/physical activity because it is fun”) and amotivation (e.g., I do PE/ physical activity but I ask myself why I do it) constructs. Responses will be provided on 7-point scales (1 = *not true for me* and 7 = very true for me). For each of the PE and out-of-school contexts, autonomous motivation scores will be computed as an average of scores on the identified regulation and intrinsic regulation items, and controlled motivation scores will be computed as an average of scores on the external regulation and introjected regulation items. Amotivation will be measured with responses provided on the same seven-point scales. Measures for autonomous and controlled motivation have demonstrated satisfactory construct validity and internal consistency statistics in previous studies [45] and measure for amotivation has demonstrated adequate level of internal consistency [47].

##### Attitudes, subjective norms, perceived behavioural control, and intentions

Students’ attitudes, subjective norms, perceived behavioural control, and intentions with respect to their future participation in physical activity will be measured using scales developed according to reported guidelines [48]. Attitudes will be measured on three items in response to a common stem: “Participating in physical activity in the next month will be…” with responses made on seven-point scales (1 = *unenjoyable* and 7 = *enjoyable*). Subjective norms (e.g., “Most people who are important to me think I should do active sports and/or vigorous physical activities during my leisure time in the next month”), perceived behavioural control (“I am in complete control over participating in physical activity in the next month”), and intentions (“I intend to do active sports and/or vigorous physical activities during my leisure time in the next month”) will be measured on two items each with responses provided on seven-point scales (1 = *strongly disagree* and 7 = *strongly agree*). Previous research has supported the construct validity and internal consistency of these measures in the context of the trans-contextual model [45].

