While there is considerable research demonstrating links between the use of autonomy-supportive intervention techniques and student autonomous motivation and adaptive outcomes in class, comparatively less research has focused on the role that autonomy support in educational settings has on students’ behaviour outside the class (e.g., participation in sport and physical activities during leisure time). Recent theory has proposed the potential mechanisms by which autonomy support in an educational context like PE may lead to participation in physical activities outside of school. Capitalizing on multiple theories of motivation, particularly self-determination theory [12] and the theory of planned behavior [26] the trans-contextual model (TCM) was developed [6]. The model (Fig. 1) outlines how teachers’ autonomy support for in-class activities in PE context transfers to autonomous motivation toward, and future intentions to engage in, leisure-time physical activity in an out-of-school context. According to the model, teachers’ promotion of students’ autonomous motivation toward physical activities in PE will lead individuals to strategically align their motivation, beliefs, and intentions toward similar activities in related contexts with those motives. A review and meta-analysis of studies adopting the model provided support for model predictions across multiple studies [10]. In particular, the analysis supported links between autonomy support from teachers and autonomous motivation in school, consistent with previous research [27, 28]. In addition, the research supported trans-contextual links between autonomous motivation in school and autonomous motivation, beliefs (attitudes, subjective norms, and perceived behavioural control), and intentions toward participation in physical activity outside of school, and actual participation in physical activity outside of school.

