The primary focus of this study is to test the effectiveness of an intervention based on the trans-contextual model in promoting out-of-school physical activity. However, we will also control for key demographic, environmental, and psychological variables that may moderate or affect intervention effects. With respect to demographic variables, we will control for effects of student’s age, gender, nationality, ethnicity and parental education level, given the potential for these variables to affect levels of physical activity and engagement in school. With respect to environmental variables, the autonomy support offered by parents and peers towards out-of-school physical activity, parental affection, and parental control may affect students’ performance and engagement in school [29, 30] and will also be considered covariates in our analysis of intervention effectiveness. Finally, we will also control for individual difference characteristics that have been shown to affect students’ motivation in previous research. These variables include grit [31] and self-discipline [32], two factors shown to be related to long-term effort and perseverance on tasks. Finally, we will also control for the extent to which students habitually perform physical activity out-of-school. The intervention may have less effect on students who have strong exercise habits, as they are already likely to exercise regularly and are unlikely to respond to motivational messages.

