##### Behavioural automaticity

Behavioural automaticity, an important component of habit, will be measured using the four-item self-report behavioural automaticity index [51] (e.g., “Physical activity is something I do without thinking”, with responses provided on five-point scales (1 = *completely disagree* to 5 = *completely agree*). This scale has demonstrated satisfactory reliability and validity in previous research [51].

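### The printed attitude stem and perceived-control item name no context, although both scores are analysed as beliefs about out-of-school activity

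*Protocol article*

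**What the plan says.** The Background (Theoretical basis for the intervention) describes the trans-contextual links as running from motivation in school to out-of-school motivation and to "beliefs (attitudes, subjective norms, and perceived behavioural control), and intentions toward participation in physical activity outside of school". The Discussion repeats that the beliefs and intentions expected to change concern activity outside school. The Data analysis section enters attitudes, subjective norms, perceived behavioural control and intentions as simultaneous predictors of out-of-school physical activity.

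The items are printed under Mediating variables (Attitudes, subjective norms, perceived behavioural control, and intentions):

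- Attitudes: "Attitudes will be measured on three items in response to a common stem". The stem is "Participating in physical activity in the next month will be", completed by the response scale.
- Perceived behavioural control: "I am in complete control over participating in physical activity in the next month".
- Intentions: "I intend to do active sports and/or vigorous physical activities during my leisure time in the next month". The printed norm item carries the same leisure-time qualifier.

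Norms, control and intentions "will be measured on two items each with responses provided on seven-point scales", and one item of each pair is shown.

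A related case is habit. The Background says the authors will "control for the extent to which students habitually perform physical activity out-of-school", while the sample automaticity item reads "Physical activity is something I do without thinking".

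**The concern.** The distinctive claim of this trial is that what teachers do in PE carries over to beliefs and behaviour outside school. To support that claim, an out-of-school belief has to be measured separately from how students feel about PE itself. The training changes PE lessons directly. If lessons become more enjoyable and nothing carries over, an attitude score that can absorb PE may still rise in the intervention arm, and the model would label that rise as a change in an out-of-school belief.

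Neither randomisation nor adjustment for the previous time point removes this. The PE component would shift after baseline and differently by arm, so it would appear as an intervention effect on the mediator.

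**Working it through.** The plan states no figure on this point, so the check sets the texts side by side.

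**1. Context of each measure as printed**

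| Measure | Context in the printed wording |
|---|---|
| Primary outcome (modified IPAQ) | Out of school, explicit |
| Autonomous motivation | PE and out of school, scored separately |
| Subjective norms (1 of 2 items shown) | Leisure time |
| Intentions (1 of 2 items shown) | Leisure time |
| Attitudes (common stem, 3 of 3 items) | None |
| Perceived behavioural control (1 of 2 items shown) | None |

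Two of the four belief and intention constructs are printed with a context and two without. The paragraph's opening sentence speaks only of future participation in physical activity, so it does not supply the missing context.

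**2. Does unqualified physical activity exclude PE in this document?** Usage is mixed. The paired motivation items offer PE and physical activity as alternatives, which suggests exclusion. Against that, the heading of the same motivation section speaks of physical activity in school as well as out of school. The accelerometer diary (Secondary outcome variables) records physical activities in both settings. A teacher item (PE teachers' provision of autonomy support and control) refers to physical activity during PE class. The term is therefore ambiguous in the plan's own language.

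**3. Consequence for attitudes.** If a student gives PE a weight *w* when answering, and the intervention changes enjoyment of PE by *d* and out-of-school enjoyment by 0, the attitude score moves by *w* × *d*. Neither quantity is in the documents. Purely as an illustration, with *w* assumed at 0.2 to 0.4 and *d* at 0.5 points on the seven-point scale:

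- 0.2 × 0.5 = 0.10 points
- 0.4 × 0.5 = 0.20 points

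This shows the direction of the error: a positive shift when the out-of-school change is zero. It does not show that any conclusion would change, because no standard deviation or mediated effect is available to set it against.

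**4. Consequence for perceived control.** Students have limited control over whether they take part in PE, so including PE mixes two kinds of control in one score. Nothing in the documents suggests that this constraint differs by arm or that the training alters it. The Background describes autonomy support as a matter of style and delivery. A constraint shared by both arms lowers or blurs the score but does not by itself create an apparent intervention effect.

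**5. Consequence for automaticity.** It is measured at pre-trial only (Procedure and data collection methods), before teacher training, and is not among the predictors listed in the Data analysis section. The intervention cannot move it.

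**The case against.** The strongest reply is that the article does not show the questionnaire students will see. The measures were translated into Finnish, only one of the two control items is printed, and headings or instructions may set the context. The article refers to an additional file for a summary of measures and promises to release the instruments. It also cites earlier support for the validity of these measures within the same model.

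Part of this stands. An unseen preamble may already resolve the matter, and the second control item may be worded differently. But the point concerns text the article chose to print, where adjacent items carry a qualifier that these lack. The statement on validity does not address context, and its source is not at hand.

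A second reply is that the damage is limited, and this stands in full. Effectiveness is judged on an outcome worded for out-of-school activity, and out-of-school motivation and the printed norm and intention items have their own context. A change confined to PE would not, through this wording, appear as an effect on behaviour or along the whole mediation chain.

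A reader might also infer that PE lessons definitely count toward these scores. The documents do not say so. They neither include nor exclude PE, and what they show is ambiguity.

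**Conclusion.** The mismatch is real on the page. The attitude stem, and so all three attitude items, and the one printed control item are not tied to the out-of-school context that the theory and the analysis model assign to them. For attitudes, a PE-only change could be misread as transfer. For perceived control, the construct is mainly blurred. The conclusion assumes that no instruction elsewhere in the questionnaire sets the context and that some students think of PE when asked about physical activity.

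The size cannot be established from the documents; the illustrative 0.10 to 0.20 points rests wholly on assumed inputs. Two stronger readings are tempting but unsupported. One is that the primary effect is at risk: its measure is explicitly out-of-school. The other is that automaticity carries the same danger: its wording is a minor mismatch in a baseline covariate and carries no risk of false transfer.

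**What to change.** Add the qualifier *during my leisure time*, already used in the same paragraph for norms and intentions, to the attitude stem and to both perceived-control items. Alternatively, set that context in the instructions above these items and say so in the protocol. If the Finnish questionnaire already does this, one sentence in the protocol settles the point.

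If data were collected without the context, report attitudes and perceived control as general physical-activity beliefs and do not use them as evidence of trans-contextual transfer. That evidence would then rest on the context-specific measures.

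The automaticity wording can be aligned with its stated out-of-school purpose at the same time, but this is optional tidying.

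The cost is a few words in the student questionnaire and a slight departure from earlier item wording, a kind of change the plan already accepts in modifying the IPAQ.

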#### Additional measures

##### Observation of teacher autonomy supportive behaviours

Teacher’s use of autonomy-supportive behaviours in their lessons will be assessed using the tool for observing autonomy-supportive behaviours in teachers (TOAST) developed specifically for this study. The tool is a modified and extended version of checklist [49] for rating teachers’ autonomy-supportive and controlling behaviours in classroom contexts. The tool was augmented to include additional content based on the list of autonomy supportive and controlling behaviours identified in previous research [18]. The checklist was also developed to closely correspond to the autonomy supportive behaviours and strategies targeted in the autonomy support training program. The tool comprises three main categories of teacher behaviour: providing instructions, praise and encouragement, and dealing with misbehaviour. Each category is coded as autonomy supportive or controlling. Two additional categories, links with out-of-school physical activity and provision of an explanation or rationale, are coded as autonomy supportive only. The tool requires observers to note the frequency of behaviours displayed by the observed teacher in each category. Overall autonomy supportive and controlling behaviours in the first three categories, and autonomy supportive behaviours in the final two categories, are calculated by summing the frequencies of the observed behaviours in each category over the observation period. The open-source BORIS software is used for coding observations [50]. Research assistants blind to the purpose of the study will be trained by project researchers to code of the audio recordings from the lessons of participating teachers’ at baseline and at the scheduled follow-up data collection occurrences.

##### Behavioural automaticity

Behavioural automaticity, an important component of habit, will be measured using the four-item self-report behavioural automaticity index [51] (e.g., “Physical activity is something I do without thinking”, with responses provided on five-point scales (1 = *completely disagree* to 5 = *completely agree*). This scale has demonstrated satisfactory reliability and validity in previous research [51].

##### Grit

Student’s grit, defined as self-rated trait-level perseverance and passion for long-term goals, will be measured using 12-item grit scale [31] (e.g., “I have overcome setback to conquer an important challenge”) with responses provided on four-point scales (1 = *not like me at all* and 4 = *very much like me*). The scale has demonstrated adequate construct and predictive validity in previous research in school contexts [52].

##### Self-discipline

Students’ self-discipline will be measured using the 10-item self-discipline scale (e.g., “I tend to carry out my plans”) from the IPIP-HEXACO scales [32]. Responses will be provided on four-point scales (1 = *not like me at all* and 4 = *very much like me*). Research has demonstrated the reliability and predictive validity of this scale in school contexts [52].

##### Perceived parental affection and control from parents

Students’ self-reports of their parents’ or legal guardians’ provision of affection, behavioural control and, psychological control will be measured using three scales taken from the modified version [29] of the child rearing practices report (CRPR) [53]: the seven-item parental affection scale (e.g., “My mother/father/legal guardian respects my opinions”), the six-item parent behavioural control scale (e.g., “When my mother/father/legal guardian gets angry, (s)he also shows it”), and the four-item parent psychological control scale (e.g., “My mother/father/legal guardian often reminds me of all the things, (s)he has done for me”). Responses will be provided on seven-point scales (1 = *not at all true* and 7 = *completely true*). Previous research has supported the construct validity and reliability of the scales [54].

##### Perceived autonomy support by parents (or legal guardians) and peers towards out-of-school physical activity

Students’ perceptions of autonomy support from their parents (or legal guardians) and peers will be measured using a four-item scale (e.g., “I feel that my parent(s)/guardian(s)/peers offer(s) me with choices, options, and opportunities to do active sports and/or vigorous exercise”) based on the PASSES [44]. Responses will be provided on 7-point scales (1 = *strongly disagree* and 7 = *strongly agree*). The measure has demonstrated adequate reliability [45].

#### Teachers’ measures

##### PE teachers’ provision of autononomy support and control

Teachers’ self-report of their provision of autonomy support to students in PE lessons will be measured on an adapted six-item version of PASSES (e.g. “I feel that I provide choices and options to my physical education students”) [44]. We also developed an additional item for autonomy support scale to assess teachers’ self-reported provision of autonomy support for student’s participation in leisure time physical activity (“I encourage my PE students to think about how physical activity during PE class can be useful to them during their free time physical activity”) and provision of a rationale for students’ participation in PE (“I feel that I provide choices and options to my physical education students”). Similarly, teachers self-report of their use of controlling behaviours in PE lessons will be measured using an adapted three-item version of the teacher social context questionnaire (e.g., “I always have to tell my PE students what to do”) [55]. Satisfactory psychometric properties have been reported for the original versions of both measures [44, 55]. Responses to items from both scales will be provided on seven-point scales (1 = *completely disagree* and 7 = *completely agree*).

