### Objectives

The purpose of the current protocol article is to report the development of a school-based intervention based on the trans-contextual model to promote secondary school students’ physical activity participation by fostering autonomous motivation (the PETALS trial). The trial will adopt a cluster-randomized waitlist-control design, and participants will be teachers of lower-secondary school PE classes and their students. The intervention will involve initial training of PE teachers of lower-secondary PE classes on the use of autonomy support strategies in their regular lessons, followed by an implementation period in which teachers apply their training in regular PE classes. Effects of the intervention will be evaluated through changes in subsequent follow-up measures of participating students’ physical activity levels and trans-contextual model variables relative to pre-trial baseline measures. We will also evaluate effects of the intervention on PE teachers’ autonomy-supportive behavior measured using self-report and observation. We will also control for support for autonomy from parents and peers. Other salient demographic and individual difference variables will be also controlled for. We expect the research will provide formative evidence of an effective, replicable, low-cost behavioural intervention, which will help in developing long-term participation in physical activity in young people. In addition, key deliverables of the research will be a set of training materials and an intervention manual, which will provide step-by-step accessible instructions on how to implement the intervention and can be disseminated to schools with no specialist knowledge and minimal cost.

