### Intervention

#### Autonomy support intervention group

Teachers in schools allocated to the intervention condition will receive the twelve-hour interactive autonomy support teacher-training program developed specifically for this study. The program aims to familiarize PE teachers with techniques and strategies aimed at promoting students autonomous motivation toward out-of-school activities. The program focuses on six sets of autonomy-supportive strategies and techniques: Taking students’ perspective, using non-controlling and informational language, providing a rationale, displaying patience, providing choices, and accepting negative emotions and feelings. The techniques are adapted from the strategies identified in previous autonomy support training programs [34–37]. The training will be delivered by two trained teacher trainers with extensive experience of PE and teacher education. The trainers will undergo a familiarization session with the core research team in which they will be introduced to the training material (manual, power point presentations, supportive material) and provided with instruction on how to deliver the program prior to implementation of the training. A summary of session content and related delivery techniques are presented in Table 1.

**Table 1 Tab1:** Description of teacher training program: Content and matched behaviour change techniques for each session

Session topic	Content	Behaviour change techniques^a^
1. Introduction and added value of the training to teaching practice	Introduction and warm up activities Information on the added value of the training and expectations Explore current supportive style and reflection Why autonomy support matters Introduction to self-determination theory	Social support (unspecified) Social support (practical) Discrepancy between current behaviour and goal Shaping knowledge Information about social and environmental consequences Imaginary reward
2. Autonomy supportive techniques: Description and benefits for students and teachers	Basics of the autonomy supportive teaching techniques: Definitions and implementation examples Using autonomy supportive techniques: Benefits for students and teachers based on previous research results	Demonstration of the behaviour Shaping knowledge Information about social and environmental consequences Behavioural practice/rehearsal

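### The printed teacher self-report item for giving a rationale repeats the existing choice item, and the text announces one added item but describes two

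*Protocol article*

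**What the plan says.** In the protocol article, under Teachers' measures (PE teachers' provision of autonomy support and control), teacher self-report rests on an "adapted six-item version of PASSES (e.g. “I feel that I provide choices and options to my physical education students". The next sentence introduces the extension: "We also developed an additional item for autonomy support scale to assess teachers’ self-reported provision of autonomy support for student’s participation in leisure time physical" (cut here before its noun). For this content it prints a separate item about linking PE to free time. The same sentence then gives a second content, "provision of a rationale for students’ participation in PE (“I feel that I provide choices and options to my physical education students".

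Three other places bear on the point:

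- The description of the autonomy support intervention group lists the six trained sets of techniques as "Taking students’ perspective, using non-controlling and informational language, providing a rationale, displaying patience, providing choices, and accepting negative emotions and feelings".
- The description of the lesson observation tool (TOAST) states: "Two additional categories, links with out-of-school physical activity and provision of an explanation or rationale, are coded as autonomy supportive only".
- The Objectives commit the trial as follows: "We will also evaluate effects of the intervention on PE teachers’ autonomy-supportive behavior measured using self-report and observation".

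**The concern.** The sentence printed for the rationale item asks whether the teacher offers choices. It does not ask whether the teacher explains why an activity is done. The protocol trains rationale giving and choice as two different techniques, so by its own definitions one cannot stand in for the other.

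If the printed wording is what teachers answer, two things follow for the self-report measure. The added item carries no information on whether training changed rationale giving, and the choice content appears twice. If the added items are pooled with the other six, the score leans toward choice. Two identical items will also tend to correlate highly, which can make internal consistency look better than it is. The mismatch between one announced item and two described leaves the length of the scale unclear as well.

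The article also undertakes, in its Discussion, to make measures available so that others can replicate the study. A wrong printed item would mislead anyone who works from this text.

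**Working it through.** The protocol gives no figure to reproduce here. The check compares wordings and then works out item weights.

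**Step 1: compare the items printed in the teacher-measure section.**

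| Order | Construct named in the text | What the printed sentence asks |
|---|---|---|
| 1 | Sample item of the six-item PASSES | Offering choices and options |
| 2 | Added: support for leisure-time activity | Linking PE to free-time activity |
| 3 | Added: rationale for taking part in PE | Offering choices and options |

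An exact character comparison of sentences 1 and 3 returns a match. No other wording for a teacher self-report rationale item appears in the article.

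**Step 2: check whether the protocol treats the two constructs as one.** It does not. The intervention section lists rationale and choice separately among the six sets of techniques, and TOAST gives rationale its own observation category.

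**Step 3: count the items.** The text speaks of one additional item but names two contents and prints two sentences. Read by content, the scale has 6 + 2 = 8 items. Read literally, it has 6 + 1 = 7.

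**Step 4: item weights.** The section states no scoring rule. Assume an unweighted mean or sum over all items, used as printed. With k items, each has weight 1/k and a duplicated item has weight 2/k.

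| Items (k) | Intended weight of choice item (1/k) | Weight if printed twice (2/k) |
|---|---|---|
| 8 | 1/8 = 12.5% | 2/8 = 25.0% |
| 7 | 1/7 = 14.3% | 2/7 = 28.6% |

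Under either count the weight of that item doubles. If the added items are scored separately from the six, there is no double weighting, but the item labelled as rationale still measures choice.

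**Step 5: limit of the calculation.** Only one of the six PASSES items is printed. The zero contribution to rationale is therefore established for the added item only, not for the whole scale.

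**The case against.** The strongest reply is that this is a copying slip in the article and not a flaw in the instrument. The text names the intended construct and says an item was developed for it, and a team would hardly present as new a sentence it had just quoted as an existing item. The questionnaire is not shown: the article refers to an additional file for a summary of measures and promises to release the instruments. It also says that self-report outcome measures were translated into Finnish, so if that covers this scale, teachers did not answer the English sentence. This reply is plausible and cannot be excluded. It makes the measurement consequences conditional, but it leaves the printed text wrong.

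A second reply is that the measure is peripheral. Teacher self-report is not the primary outcome, is not listed under the secondary outcomes or mediators, and is in neither the power model nor the main model. The perceived autonomy support in those models is the students' own report on an 18-item scale. At most one item answered by 29 teachers is affected. This stands in full and sets the size of the point.

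A third reply is that rationale giving is assessed elsewhere. TOAST codes it from audio recordings, the coders are blind to allocation, and the monitoring plan bases fidelity of delivery to students on lesson observation. This also stands.

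A reader might infer that teachers' rationale giving goes unmeasured and that choice is definitely counted twice. The document supports neither statement: observation covers the technique, an unprinted PASSES item may touch on it, and double counting needs both the printed questionnaire and a pooled score.

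**Conclusion.** The textual error is certain. The section prints an existing choice item as the new rationale item and miscounts the additions. It matters enough to correct because the Objectives name teacher self-report as one of two ways of evaluating the effect on teachers.

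The consequence is conditional. If the questionnaire is as printed, the added item does not capture self-reported rationale giving and the choice item appears twice. The doubling to 25% (eight items) or 28.6% (seven items) further assumes an unweighted, pooled score, which the protocol does not specify. Any inflation of internal consistency has not been quantified.

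The point is minor. It touches an ancillary teacher measure and does not alter the primary outcome, the mediators, the main model or the sample size. It is better read as a probable reporting slip to be verified than as a deliberate design choice.

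**What to change.** Check the teacher questionnaire actually used, then take one of three routes:

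1. **Only the article is wrong.** Print the actual rationale item and state that two items were added to the six.
2. **The questionnaire carries the duplicate and data are not yet collected.** Replace the second copy with an item asking whether the teacher gives students reasons for the activities in PE, and state the total number of items.
3. **The questionnaire carries the duplicate and data are collected.** Drop the second copy before scoring, report that the added item did not cover rationale, and judge that technique from the TOAST rationale category.

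The cost is one item wording or one scoring rule. No further participants or procedures are needed.
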